### Pectoralis Major Stretching

To start, the patient is placed in the prone position, and the therapist stands at the side of the patient, holding the patient’s forearm with one hand and securing the scapula with the other. The therapist ensures that the patient’s sternum does not leave the bed during retraction and that the shoulder joint is abducted 45°, 90°, and 135°. The therapist flexes the patient’s elbow and raises the upper arm upward as far as possible, keeping the forearm horizontal. Note that by varying the angle of abduction of the upper limb, the muscle fibers of the pectoralis major can be stretched in different parts of the body. A small angle of abduction of 45° mainly stretches the muscles located in the clavicular region (Figure 2f); a large angle of abduction of 135° mainly stretches the muscles located in the lower thoracic ribcage (Figure 2e); when stretching the muscles in the sternal region of the pectoralis major muscle, it can be taken to the 90° position for stretching (Figure 2d). The procedure is as follows:

Step 1: The therapist first raises the patient’s upper arm upward as much as possible, static-stretching for 10 seconds.Step 2: The patient is then guided to push the shoulder downward and hold for 6 seconds.Step 3: After isometric contraction, the muscle is induced to relax, and the patient adjusts their breathing.Step 4: As the patient exhales, the therapist moves the patient’s upper arm upward away from the bed with greater amplitude, maintains the position for 30 seconds, and then relaxes it.Step 5: The therapist stretches the patient’s pectoralis major muscle to its maximum amplitude once again and maintains the position for 10 seconds.

### Sternocleidomastoid Muscle Stretching

To start, the patient is placed in the supine position, pain free, with the neck lengthened. The head is rotated to the left as far as possible. The procedure is as follows:

Step 1: The therapist first static-stretches the patient’s sternocleidomastoid muscle for 10 seconds (Figure 2g).Step 2: The therapist holds the patient’s head with one hand, puts the other hand on the patient’s right ear, guides the patient to try to slowly rotate the head to the right, and then applies resistance to maintain confrontation for 6 seconds.Step 3: After isometric contraction of this muscle, the patient relaxes and adjusts their breathing.Step 4: On exhalation, the patient rotates their head to the left at a greater magnitude and holds it for 30 seconds and then relaxes.Step 5: The patient again stretches passively in the left rotational position to the maximum magnitude and holds the position for 10 seconds.

### Pectoralis Minor Stretching

To start, the patient is placed in the supine position, and the therapist stands on the side of the patient’s body, holding the patient’s hand with one hand and placing the other hand on the front of the patient’s shoulder. The therapist’s hand exerts force to bring the patient’s shoulder close to the bed, causing the scapula to move against the back and down. The procedure is as follows:

Step 1: The therapist first presses down on the front of the patient’s shoulder, static-stretching for 10 seconds (Figure 2h).Step 2: The therapist guides the patient’s shoulder upward to force against the maintenance of 6 seconds.Step 3: The muscle undergoes isometric contraction, followed by relaxation, and the patient adjusts their breathing.Step 4: During exhalation, the patient increases the range of motion to bring their scapulae closer to the bed surface, causing the scapulae to move posteriorly and inferiorly. To guide this movement, the therapist can instruct the patient to “direct their scapulae toward the back pocket of your opposite-side trousers.” The patient maintains this position for 30 seconds and then relaxes.Step 5: The therapist once again stretches the muscle to its maximum magnitude to maintain a 10-second hold.

### Obliques Muscle Stretching

To start, the patient is placed in the supine position, and the therapist places one hand on the patient’s head above the left ear and the other hand on the left shoulder to immobilize the left shoulder. The procedure is as follows:

Step 1: The therapist fixes the patient’s left shoulder with one hand and static-stretches the head toward the right shoulder with the other hand for 10 seconds (Figure 2i).Step 2: The patient is then guided to move the head forcefully against the direction of the static stretch, trying to get closer to the left shoulder for 6 seconds.Step 3: The muscle undergoes isometric contraction, followed by relaxation, and the patient adjusts their breathing.Step 4: When the patient exhales, the therapist allows the patient to actively do their best to bring their right ear closer to the right shoulder with a greater magnitude, with the tip of the nose all the way up to the ceiling; maintain the position for 30 seconds; and then relax.Step 5: The therapist stretches the patient’s obliques muscle to the maximal magnitude once again and maintains the position for 10 seconds.

The obliques are divided into anterior obliques, middle obliques, and posterior obliques. The starting position of the head is different, so it is necessary to stretch the anterior and middle obliques individually through the rotation of the head: left anterior oblique muscle’s starting position, neck right lateral flexion; head left rotation 45°; left posterior oblique muscle starting position, neck right lateral flexion; and head right rotation 45°.

Care is taken during stretching to ensure that the patient does not produce limb movements during isometric contractions. Compensatory movements are avoided, and normal breathing is required. Appropriate resistance is given by the therapist, who ensures that the full range of stretching remains painless [21].

#### Step 2: PNF Muscle Training

At the end of the PNF retraction, the patient takes a sitting position. The therapist touches the patient with their bare hands and stands behind them. Next, the therapist gives short instructions to the patient to perform forward flexion, backward extension, left lateral flexion, and right lateral flexion of the neck using the following three techniques flexibly [22]: antagonistic muscle reversal, isotonic combination, and neck diagonal movement.

### Antagonistic Muscle Reversal

The steps are as follows:

Step 1: If the therapist applies resistance to the patient’s cervical flexor muscle group, the instruction is, “Do not tilt your head back now.”Step 2: When the patient’s cervical flexor muscle group contracts, the therapist maintains resistance with one hand, while the other hand squeezes and counteracts the posterior extension of the neck, with the instruction “Do not tilt your head back now.”Step 3: When the patient responds to the new resistance, the therapist places the hand that resisted the anterior cervical flexion to the extensor side to resist the posterior extension of the neck.Step 4: Finally, the patient keeps the neck stable; the instruction is, “Now do not lower your head and do not tilt it.”

The speed and frequency of reversal movements vary from person to person. They can start slowly until the patient is stable. Only small movements are allowed during the process.

### Isotonic Combination

The steps are as follows:

Step 1: If the patient fights against the resistance applied by the therapist, the neck is flexed from a neutral position to the left side (centripetal contraction) and the head is tilted to the left.Step 2: When the patient’s neck reaches the end of left lateral flexion, they are asked to remain stable in this position, with the instruction “Stop and hold it here.”Step 3: When stability is reached, the therapist has the patient move slowly toward the starting position (centrifugal contraction), with the instruction “Now let me push you into lateral flexion to the right, but slowly.”

The therapist’s hand remains in the same position. This technique can be combined with antagonistic muscle reversal.

### Neck Diagonal Movement

The steps are as follows:

Step 1: The patient resists the therapist’s resistance.Step 2: Start with the neck in forward flexion, then left lateral rotation, and left lateral flexion and end with the neck in backward right lateral rotation and right lateral flexion.Step 3: Repeat the movements in step 2 in the opposite diagonal direction.Step 4: Alternate steps 2 and 3 and perform them three times on each side.

The PNF technique will be performed once a day [23]. The patients will be instructed to adopt a correct sitting posture and try to avoid prolonged neck flexion.

#### Group 2: The Tuina Group

The tuina group will receive TCM therapy with tuina for 30 minutes in each session. The therapist will administer each session with nine steps to ease neck pain and improve neck function. These steps are based on the principles of relaxing tendons, removing blood stasis, clearing the meridians, restructuring, expanding tendons, assisting movement, and promoting dispersal. The specific protocol used is described next, and the specific procedure is illustrated in Figure 3:

Pressing and kneading to loosen the tendons: Techniques such as one-finger Zen pushing, the holding method, and the dialing method are used on the neck, posterior occipital region, and shoulder region to relieve muscle spasm and improve blood circulation. The treatment sequence starts from the top and goes down, from the center to both sides, from the healthy side to the affected side, using gradually increasing force and depth to fully relax the neck, the posterior occiput, and the shoulder (Figure 3a).Trigger reset: If the spinous process is deviated, the cervical spine can be positioned to rotate the trigger (Figure 3b).End lifting for chaos: If there is rotation of the cervical spine in the coronal and sagittal axes, end-lifting of the neck can be performed (Figure 3c).Lateral trigger assistance: If there is a functional limitation of cervical lateral flexion, the cervical lateral trigger can be performed (Figure 3d).Symptomatic treatment: This involves pointing, kneading, and flicking the following acupoints to clear the meridians: *Fengchi* (GB 20), *Fengfu* (GV 16), *Jianyu* (LI 15), *Jianjing* (GB 21), *Tianzong* (SI 11), *Zhongzhu* (TE 3), *Jianzhen* (SI 9), *Jiequan* (EX-UE 12), and *Houxi* (SI 3).Symptomatic treatment helps activate the meridians and regulate Qi and blood circulation (Figure 3e).Spot-kneading of pain points: Focusing on spot kneading at the pain point areas of the neck and shoulder helps invigorate blood circulation, remove blood stasis, relieve spasms, and break up adhesions (Figure 3f).Drawing and stretching decompression: Cervical drawing and stretching are performed to reduce the pressure on the intervertebral discs; increase the intervertebral space; enlarge the intervertebral foramen; and reduce compression on the nerves, vertebral arteries, and spinal cord, promoting the rehabilitation of injured tissues.Shaking to assist mobilization: Neck shaking can be done to restore cervical flexion, extension, and rotation.Pushing and rubbing to disperse Qi and blood, warming the meridians and channels: Side strikes on the shoulders can be performed to relax the tendons and channels [24].

**Figure 3 figure3:**
[figure not shown]
TCM therapy with tuina: (a) thumb plucking, (b) cervical spine positioning rotary trigger, (c) cervical end lift, (d) lateral cervical trigger, (e) fishbone rubbing, and (f) tap and rub pain points. TCM: traditional Chinese medicine.

#### Group 3: The Combined (PNF+Tuina) Group

The combined group will first receive 30 minutes of PNF, followed by 30 minutes of tuina therapy; thus, the total time will be approximately 60 minutes. The PNF technique is the same as that administered to the PNF group. Tuina therapy is the same as that administered to the tuina group.

#### Outcome Measurements

Two self-report tools and two detectors will be used to measure the outcomes. The VAS and NDI scores will be used as the primary outcome measures. Cervical active joint mobility measured with the MicroFET3 Portable Muscle Strength Test and Joint Mobility Meter and muscle physical properties tested with the Myoton Muscle Tester will be used as secondary outcome measures. Pain, cervical active joint mobility, cervical spine dysfunction, and muscle physical property measurements will be performed during the first week (preintervention) and after 4 weeks’ treatment.

#### Primary Outcome Measurements

##### Visual Analogue Scale

The VAS will be selected to evaluate the pain level of patients in this experiment. The patients will be asked about the maximum level of neck and shoulder pain they experience in their daily lives. The pain will be recorded as a whole number from 0 to 10, with 0 representing no pain and 10 representing the maximum pain that has become intolerable. The pain level increases gradually from 0 to 10 [25].

##### Neck Disability Index

The NDI is a scale selected to assess patients’ cervical spine function, including both symptoms related to neck pain (eg, pain intensity, headache, concentration, and sleep) and the ability to perform activities of daily living (eg, personal care, lifting heavy objects, reading, working, driving, and recreation). Each item has a minimum score of 0 and a maximum score of 5. Higher scores indicate more severe cervical spine dysfunction. The NDI score is calculated according as [sum of scores for each item/(number of items completed × 5)] × 100. An NDI score of 0%-20% indicates mild dysfunction; 20%-40%, moderate dysfunction; 40%-60%, severe dysfunction; 60%-80%, very severe dysfunction; and 80%-100%, complete dysfunction (the patient should be examined in detail to see whether there is any exaggeration of symptoms).

#### Secondary Outcome Measurements

##### Cervical Active Joint Mobility

Cervical spine mobility will be tested using the MicroFET3 Portable Muscle Strength Test and Joint Mobility Meter. Cervical joint mobility is classified into flexion, extension, left lateral flexion, right lateral flexion, left rotation, and right rotation. Its normal reference range is as follows: forward flexion 35°-45°, backward extension 35°-45°, left and right lateral flexion 45° each, and left and right rotation 60°-80° each.

For measurement, the patient takes a sitting position, keeping the thoracolumbar spine straight. The instrument is worn on the head. Next, the patient performs cervical anterior flexion, posterior flexion, right and left flexion, and left and right rotation movements to measure cervical spine mobility. This will be performed before the overall posture measurement. The patient will remain in a neutral position: facing forward, eyes flat, and jaw inward.

##### Muscle Physical Properties

MyotonPRO (Myoton AS) is a new portable muscle testing device invented by [name], a biologist at the University of Tartu, Estonia, which can accurately and efficiently reflect the physical properties of soft tissues, such as muscles, ligaments, and tendons, and is painless and easy to operate [26]. MyotonPRO is used in the evaluation and rehabilitation of musculoskeletal and neurological disorders in both domestic and foreign populations, such as healthy people and athletes. MyotonPRO is based on the principle of slight mechanical impact on soft tissues, which produces vibrations and records vibration curves and then calculates the corresponding parameters based on the vibration curves. The parameter settings and meanings of the parameters are shown in Tables 1 and 2.

**Table 1 table1:** MyotonPRO parameter settings.

Parameter setting	Value
Maximum spectrum (Hz)	450
Impact time (seconds)	15
Delay time (seconds)	0.7
Scanning mode	Multiple (10 times)

**Table 2 table2:** Meaning of MyotonPRO parameters.

Parameter	Meaning
Muscle tone (Hz), F	The higher the F value, the higher the muscle tone or pressure within the muscle.
Muscle hardness (N/m), S	The higher the S value, the greater the muscle hardness.
Muscle elasticity, D	The higher the D value, the poorer the muscle elasticity (amplitude; logarithmic decrement).

The use of this device requires the tester to hold the handle and align the probe of the device vertically with the muscle fibers of the target muscle. The probe head needs to be perpendicular to the horizontal plane and gently and slowly pressed down. When pressed to the depth set by the instrument, the instrument starts to launch a slight impact and a subsequent rebound vibration of the probe. The tester should keep the instrument in the same position. When the impact and probe rebound vibration are over, the test ends. The damped vibration frequency, the damped decay rate, and hardness on the display are read and the three values recorded. The same muscle will be tested three times, and the average will be used as the calculated value. The tests before and after the experiment will be operated by the same tester, who is not aware of the grouping. The tension, hardness, and elasticity of the upper trapezius muscle will be tested with the MyotonPRO Digital Muscle Function Assessment System (Myoton AS).

#### Safety Evaluation

AEs refer to unexpected responses that occur during or after treatment, which can lead to hospitalization or even threaten life. The trial will be suspended immediately if we encounter AEs. The efficacy and safety of the intervention will be evaluated with 4 weeks of unsupervised follow-up, during which the patients will only receive routine neck care. At weeks 4 and 8, they will be contacted over the phone regarding their physical condition of neck pain. In addition, evaluators will be updated with the patients’ clinical symptoms and AEs.

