### Ethical Considerations

Prior to enrollment, written informed consent will be obtained from all participants by trained research staff, with the consent document clearly outlining the study objectives, procedures, potential benefits and risks, confidentiality measures, and the participant’s right to withdraw at any time without penalty. Participant identities will be anonymized using unique study identifiers, and all data (including clinical records, assessment forms, and biological samples) will be stored on encrypted servers accessible only to authorized research personnel, while publication of results will avoid disclosing identifiable information and comply with the SPIRIT (Standard Protocol Items: Recommendations for Interventional Trials) 2025 guidelines (Multimedia Appendix 1) on data sharing (item 6). An independent Data Safety and Monitoring Board (DSMB) will oversee the trial to ensure participant safety, reviewing AE reports at predefined intervals and potentially recommending trial modifications or termination if unacceptably high risks are identified, with all serious AEs reported to the ethics committee within 24 hours of discovery in accordance with institutional policies. The study protocol has been reviewed and approved by the Regional Ethics Committee of the Affiliated Hospital of Beijing University of Chinese Medicine (approval number: BUCM-2023-078; project number: 2022BZYLL1011).

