### Dropout Criteria

The dropout criteria are as follows:

The patient quits (poor efficacy or adverse reactions), which respects participants’ rights and ensures data integrity by excluding noncompliant cases.Loss to follow-up, which minimizes missing data bias; participants with ≥50% missing follow-up data will be excluded from the final analysis.Researchers remove the patient (poor compliance, complications, or serious AEs), which ensures safety and protocol adherence (eg, severe AEs require immediate termination).

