## Results

As of the data cutoff date (May 26, 2025), 43 participants were enrolled and randomly assigned to the three treatment groups (PNF group: n=14, 32.6%; tuina group: n=15, 34.9%; combined group: n=14, 32.5%), with recruitment initiated on April 1, 2025, via hospital outpatient clinics (n=45, 65.2%) and online posting (n=24, 34.8%). All enrolled participants have initiated treatment, with an average adherence rate of 92% (measured using session attendance records), and no withdrawals have occurred due to AEs or treatment dissatisfaction. The short-term follow-up (end of intervention) for the first cohort was completed on July 30, 2025, with long-term follow-up (1 month postintervention) to be completed by August 31, 2025. The final analysis is projected to include data of all 69 participants by October 2025, with primary results planned for publication in December 2025.

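### The Safety Evaluation wording brings 'AE' close to 'serious AE' or, read the other way, suspends the whole trial on one mild event; neither suits the tolerability objective and the other safety rules

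*Protocol article*

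**What the plan says.** The only AE definition in the article is in Safety Evaluation: "AEs refer to unexpected responses that occur during or after treatment, which can lead to hospitalization or even threaten life". The next sentence sets the consequence: "The trial will be suspended immediately if we encounter AEs". It gives no threshold for seriousness, relatedness or number of events.

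Other sections handle safety differently:

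- **Ethical Considerations** gives an independent data safety and monitoring board the task of "reviewing AE reports at predefined intervals and potentially recommending trial modifications or termination if unacceptably high risks are identified". It names a separate class of events, "with all serious AEs reported to the ethics committee within 24 hours of discovery".
- **Dropout Criteria** works patient by patient. A patient may leave because of an adverse reaction, and researchers may remove a patient for complications or serious AEs. The example given there is that "severe AEs require immediate termination".
- **Introduction** (objectives and hypotheses) makes safety and tolerability the third objective and expects AE rates that are low, not zero.
- **Statistical Analysis** plans AE percentages for each group, compared by a chi-square or Fisher exact test.

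**The concern.** One sentence decides what counts as an AE and the next decides what happens when one occurs. How the first is read determines which problem follows.

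If the clause about hospitalization and threat to life limits the definition, AE means something close to serious AE. The planned per-arm table may then hold almost nothing. Soreness, dizziness or a pain flare after a session, the kind of reaction that tolerability is about, may go uncounted. The word *unexpected* points the same way, because foreseeable reactions to stretching and manipulation are not unexpected. This matters for the comparison between arms: the combined group receives about 60 minutes per session against 30 in the other two, so a difference in tolerability is plausible.

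If the clause merely describes how bad an AE can become, an AE may be mild, and the literal rule halts the trial for one such event. Staff would then have one instruction to suspend, another to manage the individual patient, and a third leaving trial-level judgement to the board.

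**Working it through.** The document states no figure on this point, so there is none to reproduce. The check is a comparison of sections, followed by two illustrations under assumed rates.

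**Step 1. Restrictive reading (only events that can hospitalize or endanger life count).**

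- Against Ethical Considerations and Dropout Criteria: both use serious AE as a class distinct from AE. Under this reading there is little left for the distinction to separate.
- Against Statistical Analysis and the third objective: the AE percentages become roughly serious-event percentages, and tolerability has no clear home in the analysis.
- Against the suspension sentence: pausing after a grave event is defensible.

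Illustration, assuming 0.1% to 0.5% of patients have such an event, with N = 69 (23 per group, Sample Size Calculation):

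- Expected events: 69 × 0.001 = 0.07 and 69 × 0.005 = 0.35.
- Chance that the AE table is empty: 0.999^69 = 0.933 and 0.995^69 = 0.708, that is 93% and 71%.

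**Step 2. Broad reading (the clause is descriptive, so mild events count).**

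- Against Ethical Considerations: the board looks at AE reports periodically and acts on unacceptable risk. A halt at the first AE leaves little to accumulate between reviews.
- Against Dropout Criteria: adverse reactions and serious AEs lead to the exit of one patient, with the trial continuing.
- Against the Introduction and Statistical Analysis: a low but non-zero AE rate and a between-group comparison both presuppose that AEs occur while the trial runs.

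Chance of at least one AE, and so of suspension, is 1 − (1 − r)^N, with r an assumed rate per patient:

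| r | N = 69 |
|---|---|
| 1% | 1 − 0.99^69 = 0.500 |
| 3% | 1 − 0.97^69 = 0.878 |
| 5% | 1 − 0.95^69 = 0.971 |

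Study Design states 102 patients instead of 69. With that number the chance is 64% at 1% and 99.5% at 5%.

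Turned round, so that no rate need be assumed: holding the chance of suspension to 10% with 69 patients requires r ≤ 1 − 0.9^(1/69) = 0.0015, or 0.15% per patient.

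**Step 3. Combine.** Steps 1 and 2 are alternatives. The text cannot produce a nearly empty AE table and a suspension for mild events at the same time.

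**The case against.** The other side has four fair points.

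1. *Unexpected* may be loose wording for untoward. The article has no list of expected reactions and no rule that they go unrecorded. Assessors record AEs (Data Collection and Monitoring), and patients are phoned at weeks 4 and 8 (Safety Evaluation). This stands. A reader might infer that expected reactions are certainly excluded from the AE table. The documents support only that, read literally, they may be.
2. The restrictive reading is the more natural one, since the suspension sentence directly follows the clause on hospitalization. This also stands. A reader might infer that the trial is bound to halt at the first mild AE. That follows only from the less natural reading.
3. A suspension is not a termination. An immediate pause pending board review can coexist with 24-hour reporting and with removing the affected patient. The sentence might even have been meant for the affected patient's treatment, although its stated subject is the trial. This weakens the conflict for grave events, but not for mild ones.
4. A journal article condenses the full protocol, where AE definitions often sit. That would answer a complaint about missing detail. Here the complaint is about a definition and a rule that the article does state.

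Two further inferences should be resisted. The Results statement that "no withdrawals have occurred due to AEs or treatment dissatisfaction" does not show whether any AE occurred, so it neither confirms nor refutes the problem. A quantified loss of power in the AE comparison is not supported either: the document gives no AE rates and makes no power claim for safety, so any such figure would reflect the rates chosen.

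**Conclusion.** The point holds as a fault in stated wording. Followed literally, Safety Evaluation either narrows AE to nearly the serious class, so that the tolerability objective may lose the reactions it most needs, or suspends the whole trial for one mild event, against the board's remit and the patient-level rules. The first reading is the more likely.

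The effect is minor to moderate and confined to safety conduct and reporting. No efficacy estimate, error rate or sample size changes. The 50%, 88% and 97% figures apply only to the broad reading and rest on assumed rates of 1%, 3% and 5% with 69 patients. The 93% to 71% chance of an empty table applies only to the restrictive reading and rests on assumed rates of 0.1% to 0.5%. The change should be made, but it is a clarification and not a threat to the trial's main conclusions.

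**What to change.** Amend Safety Evaluation as follows:

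- Define an AE as any untoward event from the first session to the end of follow-up, whether or not it is expected, serious or thought to be related.
- Define serious AEs separately, and record expectedness as a flag and not as a condition for counting.
- In the analysis already planned, tabulate all AEs and serious AEs for each arm.
- Replace the suspension sentence. Individual AEs are managed at patient level, as Dropout Criteria already provides. The trial is paused only for a serious AE judged possibly related, pending review by the board, or on the board's recommendation. Other explicit triggers would also be acceptable, provided one is written down.

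The cost is an ethics-committee clarification and revised wording on the AE form. Assessors already record AEs, so no new visits or measurements are needed. Where reactions recorded so far were screened against the narrow definition, the existing records should be re-read before the final analysis.
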